## Abstract

**Background:**

The addition of antiplatelet therapy to anticoagulant therapy in patients with stroke with non-valvular atrial fibrillation (NVAF) and atherothrombotic disease may increase bleeding risk without reducing recurrent stroke risk.

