### Study outcomes

2.5

Follow-up visits will be scheduled at 6 ± 2, 12 ± 2, 18 ± 2, and 24 ± 2 months. Each follow-up visit will be conducted by the treating physician. Blood pressure measurements and laboratory examinations will be performed. Patients will be asked about any outcomes or adverse events that occurred before the follow-up visit.

The primary outcome is a composite of ischemic cardiovascular events, including cardiovascular death, ischemic stroke, myocardial infarction, systemic embolism, ischemic events requiring urgent revascularization, and significant bleeding, as defined by the International Society of Thrombosis and Hemostasis (ISTH) criteria (15) within 2 years after randomization.

Secondary outcomes include incidences of the following events within 2 years after randomization: (1) all-cause mortality; (2) ischemic cardiovascular events (cardiovascular death, ischemic stroke, myocardial infarction, systemic embolism, and ischemic events requiring urgent revascularization); (3) all ischemic cardiovascular events (ischemic cardiovascular events, TIA, unstable angina pectoris, and progression of symptomatic peripheral artery disease); and (4) ischemic stroke; and (5) myocardial infarction and cardiovascular death.

Safety outcomes include incidences of the following events within 2 years after randomization: (1) ISTH major bleeding; (2) ISTH major bleeding and clinically relevant non-major bleeding; (3) intracranial hemorrhage.

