### Sample size estimates

2.6

The sample size was calculated based on the primary hypothesis and the results of our previous study. A retrospective study of 277 patients with NVAF and atherothrombotic disease demonstrated that the combination therapy group had a higher incidence of ischemic cardiovascular events and major bleeding than the OAC monotherapy group (33% vs. 19%/2 years, log-rank *p* = 0.04; unpublished data). Based on this result, we calculated that a maximum total sample size of 370 (equally-sized groups and the maximum number of events is 74) would be required to provide a power of 90% to detect a risk reduction in outcome events within 2 years, assuming lower event rates of 13 and 27% for each group, respectively, at an overall significance level of 2.5% with one-sided log-rank tests at an interim analysis and a final analysis (EAST® version 6.4, Cytel, Boston, MA, United States). An interim analysis was planned to assess the efficacy and futility when half the required number of events was observed. The critical values for the analyses were determined based on the Lan-DeMets error-spending method using an O’Brien-Fleming-type function with a non-binding boundary for futility. With a proposed 10% dropout rate, 400 participants will be recruited for this study.

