### Statistical analyses

2.7

Analyses will be performed based on the intention-to-treat (ITT) principle. The data will be summarized using descriptive statistics. For the primary endpoint, survival curves will be estimated using the Kaplan–Meier method and compared between the two groups using the log-rank test. Hazard ratios with 95% confidence intervals will be calculated using a proportional hazards model. A per-protocol analysis will be performed to support the conclusions derived from the ITT-based analysis. Additionally, homogeneity of the treatment effects will be exploratively evaluated with the following subgroups: age (<80 vs. ≥80), sex, anticoagulant drug (warfarin vs. direct OACs), CHADS2 score (≤3 vs. 4 vs. ≥ 5), body weight (<60 kg vs. ≥60 kg), creatinine clearance (<30 mL/min vs. 30 ~ 50 mL/min vs. ≥50 mL/min), history of ischemic stroke and major bleeding, and prevalence of carotid or intracranial artery stenosis, hypertension, diabetes mellitus, dyslipidemia, and congestive heart failure.

Secondary endpoints will be analyzed in the same manner as the primary endpoints, except for the calculation of *p* values. Safety data will be analyzed descriptively for the treated set, which consists of all randomized patients who received at least one study treatment. The detailed plan for the interim and final analyses will be prespecified in the statistical analysis plan and finalized before the database lock. All statistical analyses will be conducted at the data center in the National Cerebral and Cardiovascular Center.

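### As stand-alone outcomes, bleeding events are assigned only a descriptive analysis in the treated set, while the matching ischemic composite gets an ITT hazard ratio with 95% CI

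*Protocol article*

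**What the plan says.** The protocol article's Statistical analyses section (2.7) assigns a method and a population to each class of outcome.

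- **Primary composite** (ischemic cardiovascular events plus ISTH-defined bleeding): ITT, Kaplan-Meier curves, log-rank test, hazard ratio with 95% CI from a proportional hazards model.
- **Secondary endpoints:** handled as the primary, but without p values. The ischemic composite without bleeding is secondary outcome (2) in Study outcomes (2.5), so it gets ITT Kaplan-Meier curves and a hazard ratio with 95% CI.
- **Safety:** "Safety data will be analyzed descriptively for the treated set, which consists of all randomized patients who received at least one study treatment".

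Study outcomes places stand-alone bleeding in the third class: "Safety outcomes include incidences of the following events within 2 years after randomization: (1) ISTH major bleeding", followed by major plus clinically relevant non-major bleeding and by intracranial hemorrhage. Bleeding alone does not appear among the secondary outcomes.

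The Abstract gives the motive for the trial: adding an antiplatelet agent "may increase bleeding risk without reducing recurrent stroke risk". The Discussion describes the question as one of net clinical benefit.

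**The concern.** In many trials a descriptive safety summary is enough. Here bleeding is part of the primary endpoint and is where the Background expects monotherapy to gain. If the composite favours monotherapy, a reader will first ask whether bleeding fell, ischemic events fell, or one outweighed the other. The stated methods supply an effect estimate with its uncertainty for the ischemic part and none for the bleeding part.

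The composite result cannot fill that gap. Its hazard ratio does not show which component drove it. In a survival analysis of the composite, a bleed that follows a first ischemic event would normally add nothing. The separate bleeding analysis therefore has to carry that information, and it is the one given the weaker method and a different population.

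**Working it through.** **1. The stated methods side by side** (protocol article, 2.5 and 2.7)

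| Outcome | Population | Curves | Effect estimate | p value |
|---|---|---|---|---|
| Primary composite, bleeding included | ITT | Kaplan-Meier | HR, 95% CI | yes |
| Ischemic composite alone, secondary (2) | ITT | Kaplan-Meier | HR, 95% CI | no |
| Major bleeding; major plus clinically relevant non-major bleeding; intracranial hemorrhage | treated set | not stated (descriptive) | none stated | none stated |

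The second and third rows are the two parts of the first. They differ in population and in whether an effect estimate is promised.

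**2. The plan's event count, as a frame for scale**

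Inputs from Sample size estimates (2.6): "assuming lower event rates of 13 and 27% for each group, respectively"; "would be required to provide a power of 90% to detect a risk reduction in outcome events within 2 years"; "at an overall significance level of 2.5% with one-sided log-rank tests at an interim analysis and a final analysis"; "a maximum total sample size of 370 (equally-sized groups and the maximum number of events is 74".

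- HR under exponential hazards = ln(0.87)/ln(0.73) = 0.4425.
- Freedman, fixed design: (1.96 + 1.2816)² × ((1 + 0.4425)/(1 − 0.4425))² = 10.51 × 6.69 = 70.3, so 71 events.
- One interim analysis at half the events, with a Lan-DeMets O'Brien-Fleming-type efficacy boundary and non-binding futility, inflates this by about 1.025. The futility spending function is not named; an O'Brien-Fleming type is assumed. 70.3 × 1.025 = 72.1, so 73 events.
- Mean event rate (0.13 + 0.27)/2 = 0.20, so 73/0.20 = 365 patients.

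This is close to the stated 74 events and 370 patients (74/0.20 = 370). The planned event count is not in question here.

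**3. What a bleeding hazard ratio could show**

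The documents give no bleeding rate. Assume that bleeding makes up a share s of composite events in both arms, with 200 patients per arm and no allowance for dropout.

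- Bleeds = 200 × s × (0.27 + 0.13) = 80s.
- HR = ln(1 − 0.13s)/ln(1 − 0.27s).
- 95% CI factor = exp(1.96 × 2/√bleeds).

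| s | Bleeds | HR | CI factor | 95% CI |
|---|---|---|---|---|
| 0.25 | 20 | 0.47 | 2.4 | 0.20 to 1.14 |
| 0.33 | 26 | 0.47 | 2.1 | 0.22 to 1.01 |
| 0.50 | 40 | 0.46 | 1.9 | 0.25 to 0.86 |

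The estimate would be imprecise, but it is obtainable from the planned data without any change to the sample size.

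**The case against.** **Bleeding is already analysed inferentially.** This is correct as far as it goes. ISTH bleeding is in the primary composite and is tested and estimated by ITT there. It would be wrong to say that the trial analyses bleeding only descriptively; that holds only for bleeding as a stand-alone outcome.

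**Descriptive does not mean crude.** A reader might infer that bleeding will be reported as crude proportions that ignore unequal follow-up. The article does not say so, and Kaplan-Meier or cumulative incidence by arm is also a descriptive analysis. Even with crude proportions the distortion is small. Take a true 2-year risk of 10% (λ = −ln 0.90, over the 2 years) and assumed dropout of 5% and 15% (η = −ln 0.95 and −ln 0.85). The crude risk λ/(λ + η) × (1 − exp(−(λ + η))) is then 9.75% and 9.24%. Their ratio is off by about 5%, against a CI factor of about 2. This argument carries no weight here.

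**The two populations should nearly coincide.** This is also right. Eligibility requires that participants are already on, or have begun, an oral anticoagulant, both arms receive one, and treatment starts within 3 days of randomization. Few patients should fall outside the treated set. The missing effect estimate is the substance of the point; the change of population is secondary.

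**Benefit and harm can still be compared.** A reader might infer that the two cannot be set side by side. The text does not support that: incidence by arm is to be reported for both over the same 2 years. What is lacking is a matching effect estimate with its uncertainty.

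**The SAP may say more.** It may, since the article leaves the detailed plan to it. But the article itself fixes the method and population for safety outcomes. An SAP that follows this sentence keeps the asymmetry, and one that adds hazard ratios by ITT goes beyond it. The point therefore stands in its narrow form.

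**Conclusion.** The point holds in a limited form. The article assigns stand-alone bleeding outcomes a descriptive treated-set analysis and gives the corresponding ischemic composite ITT time-to-event estimates with a hazard ratio and 95% CI. In a net-benefit trial this leaves the two parts of the composite on unequal footing, with no between-arm effect estimate planned for bleeding.

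This is a weakness in interpretation and reporting. The primary test, its error rate and its conclusion are not affected. What would be gained is an estimate with a 95% CI of about a factor of 2.4 to 1.9 either way. That rests on an assumed 20 to 40 bleeds, split between arms in the same proportions as the composite. Intracranial hemorrhage, as a narrower outcome, would probably yield fewer events and a wider interval.

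**What to change.** Amend the safety sentence in Statistical analyses, and carry the change into the SAP before database lock:

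- Analyse safety outcomes (1) to (3) like the secondary endpoints: ITT population by randomized arm, time to first event of each type, cumulative incidence at 2 years, hazard ratio with 95% CI, no p value.
- Keep the descriptive treated-set summary as supportive.
- Present the bleeding and ischemic estimates together beside the composite result.

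The cost is three further model runs on data already collected, plus the wording. Sample size, follow-up and the error rate of the primary test do not change. The one drawback is that the intervals will be wide, and the report should say so.

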### Safety and data monitoring body

2.8

Data management, statistical analysis, and monitoring will be performed by the Department of Data Science at the National Cerebral and Cardiovascular Center in Suita, Japan. An independent Data Safety Monitoring Board (DSMB), comprising two stroke neurologists and a biostatistician, will be created to monitor the safety and efficacy of the study. The DSMB will recommend trial discontinuation/continuation or protocol amendment based on annual reviews of patient accrual, the incidence of adverse events, and interim efficacy analyses comparing the two treatment arms.

### Study organization and funding

2.9

This study is partially supported by the Japan Thrombosis Investigator Initiated Research Program (JRISTA), funded by Bristol-Myers Squibb (BMS) and Pfizer. Bristol-Myers Squibb (BMS) and Pfizer were not involved in the planning, data management, analysis, or discussion of the study results. The final trial protocol was prepared by the Protocol Committee. An independent data-monitoring committee will adjudicate new outcomes at regular intervals. The committee receives outcome information and is blinded to patient identifiers and treatment allocation.

## Discussion

3

The ATIS-NVAF is the first randomized trial to evaluate the safety and efficacy of OAC monotherapy in a population at risk for both cardiogenic embolism and atherothrombotic disease. The data obtained from this trial will be crucial for identifying optimal medical treatment for these patients.

The study design focuses on comparing OAC monotherapy with combination therapy of OAC and antiplatelet agents, without imposing any specific antiplatelet or OAC regimens, to reflect real-world situations. Since the safety profile of direct OACs in patients with end-stage renal failure has not been established (16), warfarin or warfarin and antiplatelet therapy are often used in clinical practice for patients with cardioembolic stroke, renal failure, and ischemic heart disease. This study allows the use of warfarin in the anticoagulation group to explore optimal antithrombotic treatment strategies for high-risk patients.

Recent evidence highlights that inflammation and endothelial dysfunction are key contributors to both atrial fibrillation and atherosclerosis (17, 18). In atrial fibrillation, endothelial injury promotes thrombogenesis (17). Similarly in atherosclerosis, endothelial dysfunction increases the risk of thrombotic events (19). These shared mechanisms emphasize the necessity for optimized antithrombotic therapy in patients with both conditions.

Although the ATIS-NVAF trial is designed to reflect real-world clinical practice by allowing flexibility in treatment selection, this approach introduces certain limitations. First, the open-label design of the study may introduce bias, as both patients and physicians are aware of the assigned treatments. This awareness may potentially influence patient adherence, reporting of outcomes, and clinical decision-making by physicians. Second, the selection of specific OACs and antiplatelet agents, as well as their dosage, is left to the discretion of the treating physicians within the predefined options. This variability may lead to heterogeneity in the interventions, which could affect the internal validity of the study. These limitations should be considered when interpreting the results of the ATIS-NVAF trial. Despite these challenges, the pragmatic design enhances the external validity and applicability of the findings to routine clinical practice, which is a significant strength of the study.

In conclusion, this study will be the first to assess the net clinical benefit of OAC monotherapy in patients with ischemic stroke with NVAF and atherothrombosis.
